Mounting evidence has shown that antibiotics administration could result in the dysbiosis of gut microbiota which was associated with many clinical concerns including accumulation of resistance genes [6], increased susceptibility to pathogens [7, 8], and compromised immune homeostasis and tolerance [9]. Different antimicrobial agents can influence the gut microbiota in different ways. The widespread use of the FLDs using a mixture of broad-spectrum (RFP) and mycobacterial specific antibiotics (INH, PZA, EMB) for at least 6 months is a long-term, combined, and large dose antibiotic therapy. RFP has a broad-spectrum activity against a wide range of Gram-positive and Gram-negative bacteria [6]. Even for narrow-spectrum antibiotics, drugs might affect other microbes in the body, either directly by their antimicrobial activity or by host immune system modulation [10]. Referred to previous population-based studies, 20 to 25% of TB patients suffered from gastrointestinal adverse reactions and liver dysfunction during anti-TB treatment [11], which directly damaged the intestinal mucosa and led to the reduced drug absorption and liver metabolism [12].

Recent studies carried out in TB patients indicated that standardized first-line anti-TB treatment caused acute changes in the intestinal microbiota, although information on diversity changes and the altered taxa are limited. Very few studies had taken a prospective approach and most of these studies had a cross-sectional design with small sample sizes and potential heterogeneity in study participants [13–15]. Additionally, the aforementioned evidence only clarified the acute microbiome changes within the first 2 months of anti-TB treatment. As a therapy with at least 6 months of antibiotics administration, it is of great importance to systematically investigate the long-term effect of anti-TB treatment on patients’ gut microbiota and the potential influence of gut microbiota alterations on treatment outcomes and drug-induced adverse effects. Therefore, a well-controlled prospective study is needed to provide a better understanding of these questions.

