#### Secondary objectives

To describe the baseline features of gut microbiota before anti-TB treatment among TB patients with different age, gender, health status, disease comorbidity in different regions of China.To compare the characteristics of gut microbiota in terms of diversity and taxonomic composition between TB patients at baseline and healthy controls.To describe the incidence of gut microbiota dysbiosis during anti-TB treatment and its association with adverse effects and unfavorable treatment outcomes in pulmonary TB patients through a case-control study nested in the conducted cohort.To identify the potential microbial markers of unfavorable treatment outcomes.To observe the long-term effect of TB treatment on intestinal microbiota after therapy is completed.

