### Sample size

Because of the absence of prior data on the study aims of the microbiota in a cohort study design of this topic, a pragmatic approach is chosen to determine the sample size. Based on the previous collaboration with the study sites, each site should enroll 50 eligible TB patients every year so that a patient cohort of 300 cases is expected within 2 years. Referred to the treatment failure rate (10%) in China [1], 30 patients in the conducted cohort are estimated to have unfavorable treatment outcomes. The sample size of microbiota study is usually selected empirically, a wide range of study settings indicates that 30 patients each group would likely be sufficient to assess phenotypic heterogeneity at the molecular level [21, 22].

Healthy controls will be equally recruited from the population taking routine health check-up in Sichuan and Shanghai with a total amount of 60. By assuming the rates of intestinal flora dysbiosis are 20% in TB patients [11] and 5% [23] in healthy controls [23], the sample size of 200 TB patients and 60 healthy controls has over 85% power to detect a significant difference in the composition of gut microbiota at the 5% significance level.

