### Study procedures

Patients with bacteriologically-confirmed TB are informed about the study by the study coordinators. After receiving the written informed consent, socio-demographic characteristics (date of birth, gender, education, income, etc.), behaviors (alcohol use, smoking, etc.) and clinical information (concomitant medication, physical examination results, TB severity, etc.) of the participants will be documented by a well-designed structured questionnaire.

According to the national guidelines of TB treatment in China, all drug-susceptible TB patients are recommended hospitalization (2 weeks) for the start of TB treatment. The standardized first-line treatment regimen is comprised of 2 months intensive phase and 4–6 months continuation phase. Considering different treatment stages and national regulations, enrolled TB patients will be sampled at Day-0 (important to sample BEFORE treatment), Day-14, the end of intensive-phase (usually at Month-2), Month-5, the end of the treatment and the sixth month after completion of therapy. During treatment, the disease progresses, adverse effects, TB-scores [24], clinical manifestations, drug regimen, and doses of the patients will be documented. Smear microscopy testing is performed at Day-0, Month-2, Month-5 and the end of therapy. DST testing is carried out at inclusion. Additionally, in total six fecal samples will be collected from the patients at inclusion and each scheduled follow-up visit. Subjects in the healthy control arm will have their fecal specimens collected once at inclusion. Questionnaires will be used to record the socio-demographic and behavioral information as well as the health check-up results.

The bio-specimen will be transported to the TB laboratory at the designated hospitals or local Centers for Disease Prevention and Control within 12 h after collection. Stool samples should be stored at − 80 °C until DNA extraction. Figure 1 and Table 2 provide an overview of the study flow-chart and the timeline of sample and information collection.

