#### Microbiome analysis

The raw 16S rRNA gene data will be processed to generate amplicon sequence variants (ASVs) using DADA2 program [25]. Taxonomies will be assigned using Silva [26] as the reference database. Alpha diversity (such as Observed ASVs, Chao1, Shannon, Simpson, etc.) and beta diversity measures will be analyzed using QIIME2 [27] and the Wilcoxon and Kruskal–Wallis tests will be used for statistical testing of two and multi-group comparisons, respectively. Principal coordinate analysis will be used to interrogate the robustness of group-wise clustering, and Adonis test will be used to estimate statistical significance of group-wise beta diversity [27]. Generalized linear model (GLM) will be performed to evaluate the influence factors that may affect the gut microbiota of patients, such as gender, body mass index, TB severity, age, morbidities and so on [28]. Then using GLM to estimate the dynamic changes of microbiota composition with the control of selected confounders [29]. Differential abundance analysis of ASVs will be carried out using STAMP [30] and *p*-values will be adjusted for multiple testing (FDR-adjusted Wald Test). Correlations between clinical parameters and bacterial genera will be calculated using canonical correspondence analysis or redundancy analysis [31]. Random forests approach will be performed to find the most important species as marker taxa correlating with unfavorable treatment outcomes. The data will be analyzed using the QIIME2 pipeline and R [32]. A *p*-value or q-value ≤0.05 will be considered as statistically significant.

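### The stated power of over 85% for a difference in microbiota composition belongs to a two-proportion comparison that is not planned, and its 20% input is described elsewhere in the article as an on-treatment side-effect rate

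*Protocol article*

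**What the plan says.** The Sample size section sets the 300-patient cohort pragmatically, from what the sites can recruit. It then turns to the comparison with healthy controls. The rates are introduced with "By assuming the rates of intestinal flora dysbiosis are 20% in TB patients [11] and 5% [23] in healthy controls", and the article concludes that 200 patients and 60 controls "has over 85% power to detect a significant difference in the composition of gut microbiota at the 5% significance level".

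Reference 11 appears once before, in the Background: "20 to 25% of TB patients suffered from gastrointestinal adverse reactions and liver dysfunction during anti-TB treatment [11".

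The comparison with controls is a secondary objective: "To compare the characteristics of gut microbiota in terms of diversity and taxonomic composition between TB patients at baseline and healthy controls". The timing is confirmed under Study procedures. Patients give their first stool sample before treatment starts, and for controls "Subjects in the healthy control arm will have their fecal specimens collected once at inclusion".

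Under Microbiome analysis, for the diversity measures, "the Wilcoxon and Kruskal–Wallis tests will be used for statistical testing of two and multi-group comparisons, respectively". Group differences in beta diversity are tested with Adonis, and individual sequence variants by differential abundance with false-discovery-rate adjustment.

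**The concern.** Two things do not fit together.

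- **Endpoint.** Two rates, 20% and 5%, can only feed a comparison of proportions, that is, a yes/no dysbiosis state in patients against controls. The sentence nevertheless claims power for composition, which the analysis section treats as a multivariate or taxon-level quantity and tests by other methods.
- **Input.** As the Background describes it, reference 11 reports clinical side effects in patients on therapy. The Sample size section cites it for a state of the gut flora and applies it to patients who have not yet taken a dose. On the article's own description, this is a different quantity at a different time.

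This is the only power statement in the article. If the comparison with controls shows no difference, a reader could cite it as evidence that the comparison was well powered, although no planned test of that comparison has been powered.

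**Working it through.** **Inputs.** From Sample size: patient rate 0.20, control rate 0.05, 200 patients, 60 controls, 5% significance level. Sidedness is not stated; two-sided is assumed.

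**Step 1: reproduce the stated figure as a two-proportion test (normal approximation, pooled variance under the null).**

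- Pooled rate = (200 × 0.20 + 60 × 0.05) / 260 = 43/260 = 0.1654
- SE under the null = √[0.1654 × 0.8346 × (1/200 + 1/60)] = 0.0547
- SE under the alternative = √[0.20 × 0.80/200 + 0.05 × 0.95/60] = 0.0399
- z = (0.15 − 1.96 × 0.0547) / 0.0399 = 1.073
- Power = Φ(1.073) = **85.8%**

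Other two-sided versions give 87.3% (exact enumeration of Pearson's chi-square), 86.0% (Fisher), 89.9% (arcsine) and 78.9% (continuity-corrected). So the stated figure is reproduced, as power for a binary endpoint.

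**Step 2: look for that binary test in the plan.**

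- Microbiome analysis contains no comparison of a dysbiosis proportion between patients and controls.
- Dysbiosis is an outcome only in the third secondary objective, as an incidence during treatment among patients.
- Pearson's chi-square is named once, generically, under Descriptive data.

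None of these is a baseline patient-versus-control test of dysbiosis.

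**Step 3: sensitivity to the 20%.** Same formula, control rate held at 5%, 200 versus 60. For 15%, the pooled rate is 33/260 = 0.1269, the SEs are 0.0490 and 0.0378, and z = (0.10 − 1.96 × 0.0490) / 0.0378 ≈ 0.105, which gives 54%.

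| Assumed patient rate | Power |
|---|---|
| 10% | 18.2% |
| 15% | 54.2% |
| 20% | 85.8% |
| 25% | 97.8% |

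The 10% and 15% rates are illustrative assumptions. The article's own range for reference 11 runs from 20% to 25%, but for a different quantity.

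**Step 4: what can be said for a planned test.** For a two-sided 5% Wilcoxon test of an alpha-diversity index, assuming a shift between normal distributions (efficiency 0.955 relative to the t-test):

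- Detectable shift in SD units = (1.96 + z_power) × √[(1/200 + 1/60) / 0.955] = (1.96 + z_power) × 0.1506
- 80% power: 2.80 × 0.1506 = **0.42 SD**
- 85% power: 3.00 × 0.1506 = **0.45 SD**
- 90% power: 3.24 × 0.1506 = **0.49 SD**

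Power for Adonis or differential abundance cannot be computed. The article gives no distance-based or taxon-level effect size. It gives no diversity SD either, so whether a shift of 0.42 to 0.49 SD is realistic remains open.

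**The case against.** The case for leaving the text alone has four parts.

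- **The arithmetic is right.** This stands. A reader might infer a calculation error, but Step 1 shows that there is none.
- **Reference 11 may also report a dysbiosis rate.** This stands as a limit. A reader might infer that the authors demonstrably took a side-effect rate and relabelled it. The document does not prove that. It shows one reference cited for two different quantities, at 20 to 25% in one place and 20% in the other.
- **A dysbiosis variable is planned, and a chi-square test is named.** This stands in part. It would be too strong to say that no binary analysis exists anywhere, and a condensed article may leave the dysbiosis threshold to the full protocol. But the incidence objective covers patients during treatment only, so it does not supply the test whose power is claimed.
- **The sentence decides little.** This stands and bears on severity. The cohort of 300 comes from site capacity, and the primary longitudinal objective does not rest on this figure.

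What survives all four is that the sentence attaches a power to composition that its own inputs cannot give.

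**Conclusion.** The point holds at moderate severity. The figure of over 85% is correct for an assumed 20% versus 5% binary endpoint (85.8%). It is wrong as a statement about composition, because it is not the power of any planned patient-versus-control test. As the article itself describes reference 11, the 20% is also a different quantity, at a different time, from what the baseline comparison needs. This part rests on the Background's description alone.

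A reader might infer that the comparison with controls is underpowered, or that the 300-patient target is unsound. The documents support neither. The power of the planned composition tests is unknown rather than shown to be low. A patient rate of 25% would raise the binary figure to 97.8%, just as lower rates reduce it. The 300 does not depend on this calculation.

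The Wilcoxon figures assume normally distributed data, a two-sided test and the stated group sizes. They cover alpha diversity only.

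**What to change.** Withdraw the claim of over 85% power for composition, and stop using reference 11 as a baseline dysbiosis rate. Replacement text could read:

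*With 200 TB patients and 60 healthy controls, a two-sided 5% Wilcoxon test of an alpha-diversity index at baseline has 80%, 85% or 90% power for a shift of about 0.42, 0.45 or 0.49 SD, assuming normally distributed data. No power is given for Adonis or differential abundance, because no effect size is available.*

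If the binary figure is kept, label it as power for an assumed binary endpoint only, and show the sensitivity table in the working above next to it.

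Two cautions for the redraft:

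- If a dysbiosis cut-off is defined, do not set it from the same controls that are then compared, for example at the 95th percentile of their distance from their own centroid. That fixes the control rate at about 3 in 60 by construction and favours a false difference.
- Do not state as fact that the 200 patients come from Sichuan and Shanghai. The article names those sites for the controls only. Two sites at 50 patients a year for two years would give 200, but that is an inference for the authors to confirm.

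The cost is one rewritten paragraph. No further patients, samples or analyses are needed.

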### Study procedures

Patients with bacteriologically-confirmed TB are informed about the study by the study coordinators. After receiving the written informed consent, socio-demographic characteristics (date of birth, gender, education, income, etc.), behaviors (alcohol use, smoking, etc.) and clinical information (concomitant medication, physical examination results, TB severity, etc.) of the participants will be documented by a well-designed structured questionnaire.

According to the national guidelines of TB treatment in China, all drug-susceptible TB patients are recommended hospitalization (2 weeks) for the start of TB treatment. The standardized first-line treatment regimen is comprised of 2 months intensive phase and 4–6 months continuation phase. Considering different treatment stages and national regulations, enrolled TB patients will be sampled at Day-0 (important to sample BEFORE treatment), Day-14, the end of intensive-phase (usually at Month-2), Month-5, the end of the treatment and the sixth month after completion of therapy. During treatment, the disease progresses, adverse effects, TB-scores [24], clinical manifestations, drug regimen, and doses of the patients will be documented. Smear microscopy testing is performed at Day-0, Month-2, Month-5 and the end of therapy. DST testing is carried out at inclusion. Additionally, in total six fecal samples will be collected from the patients at inclusion and each scheduled follow-up visit. Subjects in the healthy control arm will have their fecal specimens collected once at inclusion. Questionnaires will be used to record the socio-demographic and behavioral information as well as the health check-up results.

The bio-specimen will be transported to the TB laboratory at the designated hospitals or local Centers for Disease Prevention and Control within 12 h after collection. Stool samples should be stored at − 80 °C until DNA extraction. Figure 1 and Table 2 provide an overview of the study flow-chart and the timeline of sample and information collection.

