## Background

Tuberculosis (TB), caused by *Mycobacterium tuberculosis* (*M. tb*), has plagued humans for thousands of years and remains a major public health problem. Estimated by the World Health Organization (WHO), there were 10 million TB cases and 1.6 million TB deaths worldwide in 2017 [1]. Among them, 890,000 new TB cases (8.9%) were infected in China, with a mortality rate of 26/100,000 [1]. TB is a curable disease, and the modern TB control program recommends the strategy of directly observed treatment – short-course therapy, which is a six-month standardized treatment using first-line anti-TB drugs (FLDs) including Isoniazid (INH), Rifampicin (RFP), Pyrazinamide (PZA), and Ethambutol (EMB). This potent standardized drug regimen has contributed to an up to 90% cure rate in TB patients during the last three decades. However, the high rate of recurrence and retreatment among TB patients, the ubiquity of severe gastrointestinal adverse reactions [1, 2], and the increasing epidemic of multidrug-resistant tuberculosis (MDR-TB) all suggest that the effectiveness of anti-TB treatment in China has yet to be addressed.

Therefore, introducing new knowledge and clinical strategies to improve the therapeutic effect and clinical prognostics in Chinese TB patients is of great significance. The recent research advances in gut microbiome have shown that these bacteria are not only actively involved in the absorption of food and drugs but also produce bioactive compounds influencing the immune and hormone systems, which is essential to maintain vital functions of the healthy host [3]. Generally, the human gut microbiota shows a large degree of interpersonal diversity [4], and its composition is also affected by many factors such as geography, diet, season, lifestyle, disease state, and in particular, the use of antibiotics [3, 5].

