### Study design

This study is an ongoing multicenter, population-based prospective cohort study conducted in three TB designated hospitals in Eastern and Western China. The study aims to include 300–400 bacteriologically confirmed pulmonary TB patients. Baseline information, including demographics, socioeconomic status, laboratory tests, and disease profiles, as well as sputum and stool samples will be collected from the enrolled patients immediately after TB diagnosis. The patient cohort will be built and followed up during the first-line anti-TB treatment at Day-14, Month-2, Month-5, last day of treatment, and the sixth month after treatment. Information regarding adverse effects, disease progress, and laboratory results will be collected at each visit. Stool samples will be sent to the laboratory for 16S ribosomal ribonucleic acid (rRNA) gene sequencing to identify the alterations in gut microbiota. A comparison of gut microbiota will be performed between newly diagnosed TB patients and healthy controls to reflect the difference in baseline features. After treatment completion, a nested case-control study will be performed between patients with treatment success or failure and patients with or without adverse effects to screen the potential biomarkers from the gut microbiota indicative of therapeutic effect.

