**Fig. 1 Fig1:**
[figure not shown]
Flow-chart of participants enrollment and follow up. Note: TB, tuberculosis; MDR-TB, multidrug-resistant tuberculosis

**Table 2 Tab2:** Summary of data collection and timeline

Timeline	Day-0	Day-14	Month-2	Month-5	End of therapy	6th month after treatment
Demographics						
Age, Sex, Occupation	X					
Financial situation	X					
Health conditions						
Comorbidities	X					
Smoking status	X					
Drinking status	X					
Clinical variables						
TB diagnostic information^a^	X					
Physical examination	X	X	X	X	X	X
Renal and liver function tests	X	X	X	X	X	X
Erythrocyte Sedimentation Rata testing	X	X	X	X	X	X
Sputum smear test	X	X	X	X	X	
TB-Score	X	X	X	X	X	
Chest X-ray	X		X	X	X	
Drug susceptibility test	X					
Current medication	X	X	X	X	X	
Drug dose	X	X	X	X	X	
Adverse effect		X	X	X	X	X
Treatment outcome					X	
Biological specimen collection						
Stool sampling	X	X	X	X	X	X
Sputum sampling	X		X	X	X	

^a^*TB* Tuberculosis

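### The visit six months after therapy takes a stool sample but schedules no item on TB recurrence, retreatment or current medication, so that sample cannot be fully interpreted and later relapse cannot be examined

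*Protocol article*

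**What the plan says.** The Background gives "the high rate of recurrence and retreatment among TB patients" as one of three signs that treatment effectiveness in China needs attention. Study design sets the follow-up visits at "Day-14, Month-2, Month-5, last day of treatment, and the sixth month after treatment" and then states that adverse effects, disease progress and laboratory results are collected at every visit.

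Study procedures is narrower. It places the recording of disease progress, TB-scores, drug regimen and doses within the treatment period, and states "Smear microscopy testing is performed at Day-0, Month-2, Month-5 and the end of therapy".

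Table 2 sets out the schedule item by item:

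- The rows "Sputum smear test" and "Sputum sampling", and those for TB-Score, chest X-ray, current medication and drug dose, have their last mark at end of therapy.
- "Treatment outcome" has one mark only, at end of therapy.
- Physical examination, renal and liver function, "Erythrocyte Sedimentation Rata testing", adverse effect and stool sampling continue to the sixth month after treatment.
- There is no row for disease progress.

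The last of the secondary objectives concerns the effect of TB treatment on the gut microbiota after therapy has ended. For the outcome analyses, Study design says that "a nested case-control study will be performed between patients with treatment success or failure", with a parallel comparison by adverse effects. The microbiome analysis adds a random-forest search for taxa that mark unfavorable outcomes.

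**The concern.** The visit takes place and a sample is taken, but nothing scheduled there establishes whether the patient has had TB again, has been retreated or is taking antibiotics. Two uses of the data suffer.

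First, the long-term objective reads the sixth-month stool as the state of the gut after completed treatment. A sample from a patient with renewed disease or renewed antibiotic exposure shows something else. The protocol treats recent antibiotic use as disqualifying elsewhere: intake in the preceding three months excludes patients at entry and excludes healthy controls. The sixth-month sample has no comparable safeguard and no record that would allow one at analysis.

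Second, because outcome is recorded once, at end of therapy, the success-versus-failure comparison and the marker search cannot be tested for robustness to later relapse. Recurrence is among the problems that the Background uses to motivate the study.

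**Working it through.** **Step 1. The three places side by side.**

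| Place | Disease progress | TB-specific tests, medication and outcome at the sixth month after treatment |
|---|---|---|
| Study design | At every visit, which includes this one | Laboratory results in general; tests not named |
| Study procedures | Placed within the treatment period | Smear ends at end of therapy |
| Table 2 | No row | No mark for smear, sputum, TB-Score, X-ray, medication, dose or outcome |

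Study design cannot be carried out from Table 2 as printed. Physical examination and erythrocyte sedimentation rate do continue, so the visit is not clinically blank. Neither is bacteriological or radiological, and neither records retreatment or antibiotic use. (The smear row also carries a Day-14 mark that the text omits. That mismatch is separate and can be reconciled at the same time.)

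**Step 2. The plan's own figures (Sample size).**

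- Cohort: 3 sites × 50 patients per year × 2 years = 300.
- Expected unfavorable outcomes: 300 × 0.10 = 30, which reproduces the stated figure.
- Expected successes: 300 − 30 = 270.

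**Step 3. How many patients could be affected.** The documents give no recurrence rate. Let r be the assumed share of the 270 successes who recur within six months. The number affected is 270 × r.

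| Assumed r | Affected (270 × r) | Failures plus recurrences (30 + 270r) | Recurrences as share of that total |
|---|---|---|---|
| 1% | 2.7 | 32.7 | 8% |
| 2% | 5.4 | 35.4 | 15% |
| 5% | 13.5 | 43.5 | 31% |
| 10% | 27.0 | 57.0 | 47% |

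**Step 4. What this does to the planned comparison.** Suppose, as an extreme case, that patients who relapse resemble failures completely. The success-group mean then moves a fraction r of the way towards the failure mean, and the observed difference is (1 − r) times the difference between failures and lasting successes. At r = 2% the factor is 0.98; at 5% it is 0.95; at 10% it is 0.90. The dilution is therefore 2% to 5% over the central range.

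**Step 5. What this does to the long-term analysis.** Among the 270 successes, the same 2% to 5% of sixth-month samples would come from patients with recurrence. Antibiotic use for other reasons would add to this, but the documents give no figure for it. On average the effect is again modest, but without the data items the affected samples cannot be identified and a sensitivity analysis is impossible.

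**The case against.** The strongest reply is that the plan is consistent with its own aims. The abstract defines unfavorable outcome as adverse effect and treatment failure, the nested comparison uses the same terms, and no objective names recurrence. The Background sentence is context and not a list of endpoints: it also names multidrug-resistant TB, and such patients are then excluded. The post-therapy visit has a stated purpose, which is the microbiota. This stands.

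A reader might infer that relapsed patients are misclassified and analysed as successes. The documents do not support that. A patient who succeeds at end of therapy is a success under the stated definition, and no sentence says how a later relapse, or that patient's last stool sample, is handled. A condensed article may leave such handling to a fuller document.

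A reader might also infer that TB status is not looked at after therapy. That is too absolute, given the every-visit statement in Study design and the continuing physical examination and sedimentation rate.

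The shares of 15% to 31% in Step 3 might be read as the size of a bias. They describe a redefined outcome at an assumed rate; dilution of the planned comparison is the 2% to 5% in Step 4.

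The reply does not remove the conflict between Study design and the other two places, nor the absence from an explicit schedule of the items needed to interpret a sample on which a stated objective relies.

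**Conclusion.** The point holds as a design weakness that is cheap to repair. It is not an error in a stated analysis. Table 2 and Study procedures provide no item at the sixth month after treatment that identifies recurrence, retreatment or current medication, and the every-visit statement in Study design does not agree with them. The main consequence is for the long-term microbiota objective, whose final sample cannot be separated by renewed disease or renewed antibiotic exposure. The lesser consequence is that the outcome and marker analyses cannot be checked against later relapse.

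The size rests on the plan's 300 patients and 10% failure rate, and on an assumed 2% to 5% recurrence: about 5 to 14 of some 270 successes, with modest dilution. The true rate cannot be taken from the documents.

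**What to change.** - Reconcile Study design, Study procedures and Table 2 on whether disease progress is recorded at the sixth month after treatment and by which item.
- Add three entries to that column of Table 2: TB recurrence or retreatment since end of therapy (yes/no, with date); current medication, including antibiotics; and the TB-Score.
- Keep success versus failure at end of therapy as the main comparison. Add a sensitivity analysis, for the outcome comparison and the marker search, of sustained success against failure or recurrence.
- Report the long-term microbiota analysis with and without the samples of recurrent or retreated patients.

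The cost is slightly more data collection at a visit that already takes place, with no new visit or laboratory test. The sensitivity outcome is known six months later, and recurrence will be missing for patients lost after therapy. Leaving out recurrent patients selects on a post-treatment event and can itself bias the long-term result, which is why both versions should be shown.
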